#### Socio-demographic variables

Self-reported socio-demographic variables included age, gender, race/ethnicity, language, English proficiency, years since immigration to the U.S., marital status, educational attainment, employment status, annual household income, self-reported health literacy [49,50], and duration of diabetes. We obtained SFHP administrative and CHNSF data regarding age and gender. Preferred language is captured in both SFHP and CHNSF data, and where this preference was discrepant, we used the language reported to SFHP enrollment workers.

#### Primary and Secondary Patient-Reported Outcomes

The primary outcome variables are physical and mental functional status (SF-12) and the number of days spent in bed due to illness [51]. Secondary outcomes include diabetes self-efficacy and self-management behavior, as well as medication adherence in the preceding 7 days [52-54]. Secondary outcomes also include patient perspectives on the structure of their care, as measured by two instruments which have been translated and validated for our population in our prior work: Patient Assessment of Care for Chronic Conditions (PACIC) and interpersonal processes of care (IPC) [33,55,56].

#### Cardiometabolic Outcomes

These secondary outcomes will be analyzed on the larger set of SFHP participants randomized in the trial (N = 362), regardless of whether or not they participated in the evaluation interviews. Cardiometabolic outcomes include measures of HbA1C, LDL, and blood pressure obtained by clinical providers. Data will be derived from CHNSF electronic health record, the clinical registry database, and paper chart review. Values will be used at baseline only if obtained within one year before program enrollment. Follow-up laboratory and blood pressure values will be included only if obtained within 90 days before or after the 6-month and 12-month follow-up dates.

#### Care Delivery Processes and Utilization

Finally, for all eligible participants, we will use SFHP administrative claims data to examine measures of care delivery processes: proportion receiving blood pressure checks, laboratory testing, retinal examinations, influenza vaccination, and pneumococcal vaccination at guideline-concordant frequencies [43]. We will also examine utilization, including the frequency of emergency department visits and hospitalizations.

#### Program Engagement and Satisfaction

Using data from the ATSM system, we will assess patient engagement as measured by exposure intensity (defined as the proportion of the 27 weeks of exposure, participants replied to the weekly calls) and the proportion of weekly calls that are determined to be complete (calls answered and responses to 100% of queries), partially complete (call answered and responses to < 50% of queries), and incomplete (call answered but responses to 0% of queries) [32]. In addition, using data from the SFHP health coach database, we will analyze at the participant level the number of health coach calls that were triggered by ATSM responses; the number of calls attempted and/or completed by health coaches; and the number of action plans created and/or achieved, as reported by patients and documented in the database. We will conduct fidelity assessments to examine potential differential engagement across languages, clinics and study arms. Finally, we will assess satisfaction and perceived usefulness of the intervention as reported during evaluation interviews at 6- and 12-month follow-up.

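### The definition of a partially complete call leaves answered calls with 50–99% of queries answered in no category

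*Protocol article*

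**What the plan says.** The Protocol article, section Program Engagement and Satisfaction, takes two kinds of engagement measure from the automated telephone system.

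- The first is "exposure intensity (defined as the proportion of the 27 weeks of exposure, participants replied to the weekly calls". It does not depend on how many queries within a call were answered.
- The second is a breakdown of calls, introduced as "the proportion of weekly calls that are determined to be complete" and continuing through two further classes. The three rules are:
  - for the top class, "complete (calls answered and responses to 100% of queries"
  - for the other two classes, "partially complete (call answered and responses to < 50% of queries), and incomplete (call answered but responses to 0% of queries"

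The sentence cites a report from the earlier trial of the same type of system. Later in the section the article gives one planned use of engagement data: "We will conduct fidelity assessments to examine potential differential engagement across languages, clinics and study arms". No other section gives a lower bound for the middle class, a class for the upper band, or a rule for a call that meets two definitions.

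**The concern.** A classification of calls should put each answered call in exactly one class. The middle class here stops below 50% while the top class starts at 100%, so a patient who answers most but not all of the queries produces a call with no label. This can be expected to happen: the article describes weekly calls of 8 to 12 minutes built from rotating sets of queries, and some patients may stop part-way.

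What is at stake is the *partially complete* share and any comparison that uses it. If language groups, clinics or arms differ in how far patients get through a call, the printed rule leaves out the calls that came closest to completion. An analyst who meets the gap in the data would have to repair it then, and the plausible repairs give different shares.

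**Working it through.** There is no sample-size or power figure to reproduce. The check applies the three printed rules to every share of queries answered in an answered call.

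**Inputs** (all from Program Engagement and Satisfaction), with *p* the percentage of queries answered:

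- *complete*: p = 100
- *partially complete*: p < 50, with no lower bound stated
- *incomplete*: p = 0

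**Step 1. Whole-percent levels 0 to 100 (101 levels).**

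| p | Classes met | Number of levels |
|---|---|---|
| 0 | *partially complete* and *incomplete* | 1 |
| 1–49 | *partially complete* | 49 |
| 50–99 | none | 50 |
| 100 | *complete* | 1 |

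Check: 1 + 49 + 50 + 1 = 101. These are levels of the scale, not calls. That 50 of 101 levels are unassigned does not mean that about half of calls are.

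**Step 2. In counts of queries.** The article does not give the number of queries per call, so the following values are assumptions.

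| Queries per call (assumed) | Answer counts with no class |
|---|---|
| 5 | 3, 4 |
| 10 | 5 to 9 |
| 12 | 6 to 11 |
| 20 | 10 to 19 |

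The gap appears at every length tried.

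**Step 3. Effect on the shares.** Among answered calls, let a, b, c and d be the fractions with 0%, 1–49%, 50–99% and 100% of queries answered, so a + b + c + d = 1.

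- *Complete* share = d and *incomplete* share = a. Neither involves c.
- *Partially complete* share as printed = b, giving 0% calls to *incomplete*.
- Sum of the three shares = a + b + d = 1 − c. The shortfall is exactly the unclassified band.

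**Step 4. Effect on a comparison of groups 1 and 2.**

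- Difference in the printed *partially complete* share: b₁ − b₂.
- Difference in the share of all partly answered calls: (b₁ + c₁) − (b₂ + c₂).
- The two differ by c₁ − c₂, which is zero only if the unclassified band is equally common in both groups.

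Suppose one group has the same a and d as another but gets further through its partly answered calls, so that calls sit in c rather than b. Its printed *partially complete* share is then lower, although its engagement is better.

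**Step 5. Different repairs give different answers.** Reading the bound as under 100% gives b + c. Reading it as over 50% gives c (apart from calls at exactly 50%) and moves the gap to 1–50%. Keeping the print gives b. Nothing in the article selects among them.

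**The case against.** The strongest reply is that this is one loose bound in a descriptive process measure, in a condensed article that cites a source for its definitions. Several parts of that reply stand.

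- A reader might infer that the engagement proportions cannot be computed at all. The document does not support this. Exposure intensity does not use the classes, and the *complete* and *incomplete* shares rest on exact values once a denominator is chosen.
- A reader might infer that empty calls are counted twice. The two definitions do overlap at 0% as worded, but *partially complete* in its plain sense implies at least one response, and a specific 0% class follows it. A sensible analyst would use that class.
- A reader might infer that unanswered calls are lost. All three classes are limited to answered calls, so unanswered calls are an evident further group, and exposure intensity over 27 weeks largely captures them. Shares of all weekly calls need not sum to 100% when some calls go unanswered. Only the choice of denominator is left open.
- The fidelity assessment does not rest on this split alone. The section also lists coach calls triggered, attempted and completed, and action plans created and achieved.
- The printed bound may be a slip, and the cited source is not at hand to settle it.

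None of this fills the 50–99% gap. The article does not leave the cut-offs to a fuller document: it prints numbers, and those numbers fail to classify a foreseeable kind of call. If the bound is a slip, the text does not show which bound was meant.

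**Conclusion.** The point holds in a limited form. As printed, answered calls with 50–99% of queries answered belong to no class, so the *partially complete* share omits the nearly complete calls and can mislead in a comparison across groups. The 0% overlap is a minor drafting fault.

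The size cannot be given in calls. The whole band is lost, but the article reports no call-level data, and the band could hold many calls or very few. The bias in a group comparison equals the between-group difference in that band, so it could be nil. The conclusion assumes that the printed bound is the one applied.

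It would be wrong to carry the point over to the trial's results. Call class does not appear among the outcomes in Table 1, in the Data analyses section or in the sample size calculations, so the primary and secondary outcomes and the power are untouched.

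**What to change.** Restate the middle class as an answered call with more than 0% and less than 100% of queries answered. Alternatively, limit it to more than 0% and less than 50%, and add a separate class for 50% to less than 100%. Either version puts each answered call in exactly one class and removes the 0% overlap.

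In the same place, say whether the denominator is all scheduled weekly calls or answered calls only. If it is all scheduled calls, unanswered calls make up the remainder.

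The cost is a sentence or two. The automated telephone system is already the named data source, so no new data collection is needed. The wording should be settled before the call data are compared between groups.

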### Data analyses

We will assess the similarity of baseline characteristics between study arms using t-tests, chi-square tests, and Fisher's exact tests. We will control for any significant differences in baseline characteristics in analyses of all primary and secondary outcomes.

For each outcome, we will compare differences between study arms in 6-month changes using intent-to-treat analyses. Because this study is a quasi-experimental evaluation trial with a wait-list variant of a stepped wedge design, analyses of outcome changes will be conducted with two distinct methodologies. The first method will involve analyzing the data as if the trial was a standard intervention versus control study, comparing all participants who were randomized to the ATSM intervention (either SMARTSteps-ONLY or SMARTSteps-PLUS) versus all participants randomized to the wait-list control groups. We will use linear regression for continuous variables, logistic regression for dichotomous variables, and negative binomial models for the outcome variable of number of bed days because of its non-parametric data distribution. We will include as model covariates the baseline value of outcome variables and any socio-demographic or medical variables that may have differed by chance among the groups.

The second method will take advantage of the wait-list variant, stepped wedge design with study cross-over of participants from control to intervention [40]. It will employ a repeated measures analysis using maximum likelihood to fit the models. Because discrete external events may coincide with the time that participants cross-over from control to intervention and thereby possibly confound the within-group comparisons from the wait-list control group, secular effects in the wait-list group will be modeled first to see if a specific spline to capture non-linearities analysis is needed or if a simple linear trend exists, simplifying the analysis. Other possible covariates in the model may be calendar time, actual time of intervention exposure, and predictors of dropping out of study.

To explore the added value of the medication activation arm, both the first and second methods above will also be used to compare SMARTSteps-ONLY versus SMARTSteps-PLUS in all primary and secondary outcomes.

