### Study arms

All eligible SFHP members interested in the SMARTSteps program were assigned by SFHP through language-stratified randomization to one of four intervention statuses: SMARTSteps-ONLY, SMARTSteps-PLUS, wait-list for SMARTSteps-ONLY, or wait-list for SMARTSteps-PLUS.

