The results of this evaluation trial, when completed, must be interpreted within the following limitations. First, SFHP's phone-based population recruitment targeted different languages over time due to enrollment worker availability, with greater emphasis on Cantonese-speaking populations earlier. Thus, potential differences in intervention impact by language may relate to changes in project implementation over time. Second, because SFHP does not have medication prescribing authority for its members or authority to document within participants' medical records, the interventions will not be fully-integrated into care delivery in the context of participants' medical homes; this may limit the effectiveness of the intervention, particularly the SMARTSteps-PLUS medication intensification arm. Finally, because data for cardiometabolic outcomes relies on collection through routine medical care rather than scheduled study visits, we may not be powered to detect a modest impact of the intervention on glycemic or blood pressure control.

Improving health communication through the use of tailored, proactive HIT is one scalable vehicle to improve chronic disease care for vulnerable populations [32,33]. Focusing on improving the processes of care for vulnerable populations in under-resourced safety net settings through the application of evidence-based or evidence-informed HIT tools can have far-reaching implications for bridging the clinical care-public health divide, not only for diabetes, but for other chronic conditions and for preventive services [27]. The SMARTSteps outcomes will provide evidence regarding the real-world implementation of ATSM within a Medicaid managed care plan and provide insight into translating and scaling up HIT interventions for linguistically and culturally diverse vulnerable populations with chronic disease.

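### Covariates beyond the baseline outcome are picked by baseline significance tests, a rule that will almost never pick language, the stratification factor

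*Protocol article*

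**What the plan says.** All in the protocol article.

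- **Data analyses, opening paragraph.** "We will assess the similarity of baseline characteristics between study arms using t-tests, chi-square tests, and Fisher's exact tests". Then: "We will control for any significant differences in baseline characteristics in analyses of all primary and secondary outcomes". No threshold is given.
- **Data analyses, Method 1** (intervention versus wait-list regression). The model covariates are "the baseline value of outcome variables and any socio-demographic or medical variables that may have differed by chance among the groups". The baseline outcome value is thus fixed in advance, and everything else depends on observed differences. A significant difference and a chance difference are not the same criterion, so the two statements do not define one rule.
- **Data analyses, Method 2** (repeated measures using the crossover). Secular effects in the wait-list group are modelled first, with a spline if needed. Then: "Other possible covariates in the model may be calendar time, actual time of intervention exposure, and predictors of dropping out of study". Language is not named.
- **Study arms.** Members were "assigned by SFHP through language-stratified randomization to one of four intervention statuses". Study integrity adds that the randomisation was blocked, with the participant as the unit, and was run for each of the three languages.
- **Discussion, limitations.** Recruitment "targeted different languages over time due to enrollment worker availability, with greater emphasis on Cantonese-speaking populations earlier".

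**The concern.** Between randomised arms, a baseline p-value measures how far chance has separated the groups on a variable. It does not measure how well that variable predicts the outcome, and only prediction makes a covariate worth adjusting for. A rule based on such p-values leaves the fitted model unknown until the data are seen. With no threshold and two wordings, it also leaves room for choice afterwards.

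The rule also works against the trial's own design. Language was balanced by stratified blocking, so a test for imbalance will pass it over, yet the factor used to stratify is the one the analysis should carry. In Method 1 the price is precision and calibration. In Method 2 it can be bias, because language mix and calendar time are linked and the model has to separate a calendar trend from the treatment effect.

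**Working it through.** **The plan's own figures.** No figure in the article depends on the covariate rule. The yardstick used below is its standardised effect of 0.35 for SF-12 at 80% power. Two-sided, 1:1, with alpha 0.05 (assumed, since none is stated), this needs 129 per group, 258 in total. That agrees with the stated 260 if 260 is the number analysed. No covariate enters that calculation.

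**1. Would the rule select language?** Inputs are the language counts in Table 2: English 121, Spanish 61, Cantonese 180, total 362. Four-arm blocked randomisation within each language was simulated with block size 4 and again with 16, because the 4 × 4 description allows either reading. A chi-square test of language by arm gave p < 0.05 in 0 of 3000 trials for each block size. A random subset of 278 (the number with baseline interviews) also gave 0 of 3000, but only on the assumption that interview uptake is unrelated to arm and language.

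**2. Would it select something else?** The Socio-demographic variables section lists 12 self-reported items. Setting language aside leaves 11. If the tests were independent at 0.05, the chance of at least one significant result is 1 − 0.95^11 = 43% (with all 12, 1 − 0.95^12 = 46%). Several items are plainly correlated (language, English proficiency, ethnicity, years since immigration), so this is only indicative. It is the chance of adding a covariate by luck, not an error rate.

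**3. Method 1: cost of leaving language out.** Let R² be the share of residual outcome variance explained by language after baseline adjustment. The article gives no value, so this is an assumption. With balance by design, the true type I error of the model without language is 2 × [1 − Φ(1.96/√(1 − R²))], and the standard-error reduction from adjusting is 1 − √(1 − R²).

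| R² (assumed) | Type I error | SE reduction |
|---|---|---|
| 1% | 4.9% | 0.5% |
| 2% | 4.8% | 1.0% |
| 5% | 4.4% | 2.5% |
| 10% | 3.9% | 5.1% |
| 15% | 3.4% | 7.8% |

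Simulation with 250 analysed, 4000 runs per setting, agrees. At R² of 5%, type I error is 4.4% with language chosen by test and 4.6% with language always included. At 10% it is 3.9% versus 4.8%. Power at an effect of 0.35 is 79.5% versus 81.4% at R² of 5%, and 78.6% versus 82.2% at 10%.

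**4. Method 2: does it reach the treatment effect?** A zero true effect was simulated with four waves, 248 patients, wait-list crossover at 6 months, a random patient intercept and a linear calendar trend. The following are assumptions: the Cantonese share falls from 70% to 30% across waves, the outcome gap between language groups is 0.3, 0.5 or 0.7 SD, and the intraclass correlation is 0.5 to 0.7.

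- Language omitted: mean spurious effect of about 0.03, 0.05 and 0.06 to 0.08 SD for the three gaps.
- Language included: zero to within simulation error.

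The mechanism is that a random-intercept model estimates the calendar slope partly from differences between patients recruited at different times. Those differences include the change in language mix. The slope is then wrong within patients, and the treatment term, which switches on later in each patient's follow-up, absorbs the discrepancy. At a gap of 0.5 SD the result is 0.05/0.35 = 14% of the planned effect, and roughly 0.7 of a standard error. Its sign follows the sign of the language gap.

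**The case against.** - **The tests are not empty in the interview subset.** Willingness to be interviewed was assessed after randomisation, and 278 of 362 (77%) gave baseline interviews. A reader might infer that baseline p-values here test a null hypothesis known to be true and that language is balanced by design. The documents support that for all 362 randomised. They do not support it for the set that supplies the primary outcomes, where selective consent could also separate the arms. This stands. It does not rescue the rule, because a p-value is no better a guide to which consent-related variables matter.
- **The most useful predictor may already be in.** The baseline value of the outcome is fixed in Method 1. This stands: the complaint covers only the remaining covariates, and baseline adjustment may absorb much of any language difference, which is why the R² range starts at 1%.
- **Method 2 is protected because the crossover comparison is within patient.** This would hold if patient effects were fixed. It does not hold for a model with random patient effects, as step 4 shows. Modelling the wait-list trend first does not help, because that trend is estimated across waves with the same shifting mix.
- **Naming the stratifier is detail an article leaves to the analysis plan.** That would answer a mere silence. Here the article states a selection rule for all primary and secondary outcomes, and following it as written excludes language.

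**Conclusion.** The point holds as one that should be corrected, at moderate weight. The stated rule makes the covariate set data-dependent and will almost never admit the stratification factor in the full randomised set.

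In Method 1 the consequence is small. A reader might infer that the randomised comparison is biased. It is not, since arms were randomised concurrently within language. The loss is a slightly conservative test and up to about 8% in standard error, at the assumed upper R² of 15%.

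In Method 2 the consequence can be bias of about 0.03 to 0.08 SD. That size rests on the assumed shift in language mix, the language gap and the random-intercept model. The article says only that the mix shifted, so neither the size nor the direction can be taken as a prediction for this trial.

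**What to change.** 1. Delete the rule that covariates follow from baseline significance or chance differences, in both places in Data analyses.
2. Method 1: keep the baseline outcome value and add language (three levels) as a fixed covariate in every model. Recruitment wave is optional.
3. Method 2: include language as a main effect and make calendar time a fixed covariate instead of a possible one. Keep separate calendar trends by language as a sensitivity analysis, since only 61 enrolled members were Spanish-speaking and languages were recruited unevenly over time.
4. Interview subset: name any further covariates in advance, chosen for prognostic value or relation to consent, not by p-value.

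The cost is wording, with no change to data collection. Language takes two degrees of freedom; with wave (four waves, three more) it is five, against about 250 patients analysed. Language-specific trends would cost more, which is a further reason to keep them as a sensitivity analysis.
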